## 2. Experimental Design and Materials

### 2.1. Objectives and Endpoints

The main objective of the REFILL-PAC-HYPO trial is the evaluation of the effect of an app reminding patients receiving moderately hypo-fractionated radiotherapy for localized prostate cancer to drink water before each session of radiotherapy on the number of sessions during which the bladder volume was <200 mL. The app reminds patients to drink 300 mL of water 45 min before each radiotherapy session. The selection of these parameters was based on clinical experience and previous studies [10,11,12,14,15,16,17,18,19,20,21,22,23,24]. When considering these studies, the median time interval between water intake and radiotherapy was 45 min, and, therefore, this was selected for the REFILL-PAC-HYPO trial. Since the median amount of water was 400 mL, this amount was initially chosen for the trial. However, the centers participating noted that a considerable number of patients irradiated for prostate cancer experienced difficulties in retaining urine until the completion of their radiation session if they drank more than 300 mL before the session. Therefore, an amendment of the protocol using 300 mL instead of 400 mL was submitted to and approved by the Ethics Committee. The primary endpoint of the REFILL-PAC-HYPO trial is the number of radiotherapy sessions with a bladder volume of <200 mL at the end of treatment (20 fractions). The secondary endpoints include satisfaction with the app and the impact of participation in the trial and using the app on general attitudes towards health technology. The patients’ adherence to the app is assessed. The patients have to confirm their intake of water each day and receive a puzzle piece as a reward. Moreover, the patients are interviewed by staff members during their daily visits to the radiotherapy department regarding their time and amount of water intake.

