### 2.4. Sample Size Calculation

The primary objectives of the REFILL-PAC-HYPO trial are the assessment of the effect of an app reminding prostate cancer patients treated with moderately hypo-fractionated radiotherapy to drink water before each treatment session on the number of sessions with bladder volumes of <200 mL and to demonstrate that this number is lower when compared to a historical control group not supported by a reminder app. To allow for a skewed distribution of the primary endpoint, the Wilcoxon–Mann–Whitney test will be applied for confirmatory statistical analysis. The calculation of the required sample size is based on an article by G.E. Noether [25]. In the external historical control group consisting of 52 patients, the mean number of radiation fractions with bladder volumes of <200 mL was 16.0 (SD 5.5), and the median number was 19.0 fractions (IQR 14.5–20.0) [13]. A decrease in this mean value by roughly 30% (to 11.2 fractions) is considered clinically relevant, based on the findings from our previous study and our clinical experience [13]. For illustrative purposes, translating this decrease into a non-parametric effect size framework (assuming, for simplicity, a normal distribution) leads to a probability of roughly 0.27 that the number of fractions of <200 mL with the reminder app will be larger than without the app. Based on this effect size, a sample size of 24 patients in the prospective REFILL-PAC-HYPO trial is required for the comparison with the historical control group to ensure a 90% power to reach statistical significance with a two-sided Wilcoxon Mann–Whitney-U-test and a 5% significance level. Assuming that roughly 10% of the enrolled patients will not be eligible for the primary analysis, since they may receive less than 20 fractions, a total number of 27 patients should be enrolled in the REFILL-PAC-HYPO trial.

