#### 3.2.4. Questionnaire Regarding the App and Its Impact on Using Health Technology

At the end of the course of moderately hypo-fractionated radiotherapy, the patients will complete a questionnaire (modified according to [27,28]) regarding their satisfaction with the reminder app. If more than 20% of the patients are not satisfied, the app needs to be improved and requires modifications. If the dissatisfaction rate is >40%, the app is considered not useful. These thresholds were selected based on the protocols of previous trials by our group developed after discussions with the Ethic Committee responsible concerning this matter [29,30]. In addition, this questionnaire addresses the impact of participation in the trial, including the use of the reminder app, on the patient’s general attitude towards health technology.

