Since no comparison with the historical control group is possible regarding the secondary objectives, these analyses focus only on descriptive analyses. The patient satisfaction results will be used to decide whether the reminder app needs modification. If the dissatisfaction rate is >20%, the app needs modifications. If the dissatisfaction rate is >40%, the app is considered not useful for improving the bladder filling status of patients treated with moderately hypo-fractionated radiotherapy for localized prostate cancer.

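### The >40% dissatisfaction rule in Section 3.3 draws a conclusion about bladder filling from a satisfaction rate, and can contradict the primary analysis

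*Protocol article*

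**What the plan says.** **Role of the endpoint.** Section 2.1 makes the number of sessions with bladder volume below 200 mL, out of 20, the primary endpoint. On satisfaction it says: "The secondary endpoints include satisfaction with the app".

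**Confirmatory question.** Section 2.4 gives as a primary objective "to demonstrate that this number is lower when compared to a historical control group not supported by a reminder app". Sections 2.4 and 3.3 assign this to a two-sided Wilcoxon–Mann–Whitney test at the 5% level.

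**Satisfaction rules.** Section 3.2.4 sets the timing: "At the end of the course of moderately hypo-fractionated radiotherapy, the patients will complete a questionnaire". It then gives two thresholds: "If more than 20% of the patients are not satisfied, the app needs to be improved and requires modifications", and "If the dissatisfaction rate is >40%, the app is considered not useful". Their origin is given as "These thresholds were selected based on the protocols of previous trials by our group", after discussion with the ethics committee. The Abstract states the same two rules in the same limited form.

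**The wider version.** Section 3.3 says of the secondary objectives that "these analyses focus only on descriptive analyses". It repeats the 20% rule and then widens the 40% rule: "If the dissatisfaction rate is >40%, the app is considered not useful for improving the bladder filling status". This sentence does not refer to the primary result.

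**The concern.** A patient can find the app irritating and still arrive with a full bladder. A questionnaire on satisfaction therefore cannot show whether the app improves bladder filling. Section 3.3 nevertheless lets the questionnaire produce a negative statement on exactly that question, which the trial was sized to answer by other means.

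If the primary test is significant and dissatisfaction exceeds 40%, the article supports two opposite statements about bladder filling and gives no way to choose between them. A choice made after the data are seen would be post hoc, and it would concern the trial's main conclusion.

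The rule is also applied to an observed proportion in a very small sample, with no interval or error rate. A reader would not see how uncertain the verdict is.

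**Working it through.** **1. The plan's own sample size (Section 2.4).** Inputs: 52 historical controls, mean 16.0, SD 5.5, target mean 11.2, two-sided 5%, power 90%.
- Effect: p = Φ(−(16.0 − 11.2)/(5.5·√2)) = 0.2686, given as roughly 0.27.
- Noether: K = (1.960 + 1.282)² / [12·(0.2686 − 0.5)²] = 16.35.
- With 52 controls fixed: n = 16.35·52/(52 − 16.35) = 23.8, so 24.
- Allowing for 10% not evaluable: 24/0.9 = 26.7, so 27.

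Both stated figures reproduce. They concern the primary comparison only. The article gives no operating characteristics for the 20% and 40% rules, so there is no stated figure to check for those.

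**2. The three statements of the 40% rule.**

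| Place | Consequence of >40% dissatisfied |
|---|---|
| Abstract | app not useful |
| Section 3.2.4 | app not useful |
| Section 3.3 | app not useful for bladder filling in these patients |

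The first two can be read as verdicts on acceptability. The third is a statement about efficacy. Nothing in Sections 2.1, 2.4, 3.3 or 4 says what follows if it disagrees with the primary test.

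**3. How the rule behaves on the observed rate.** The denominator for satisfaction is not stated. It is taken here as an assumption to lie between 24 (evaluable for the primary analysis) and 27 (enrolled). The rule triggers at the smallest count r with r/n > 0.40. The trigger probability is the exact binomial tail P(X ≥ r), and the interval is Clopper–Pearson.

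| n | r | r/n | exact 95% CI | true rate 30% | true rate 35% | true rate 40% |
|---|---|---|---|---|---|---|
| 24 | 10 | 41.7% | 22.1–63.4% | 15.3% | 31.3% | 51.1% |
| 25 | 11 | 44.0% | 24.4–65.1% | 9.8% | 22.9% | 41.4% |
| 26 | 11 | 42.3% | 23.4–63.1% | 12.5% | 27.8% | 47.9% |
| 27 | 11 | 40.7% | 22.4–61.2% | 15.7% | 33.0% | 54.2% |

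The last three columns give the probability that the rule triggers. At n = 24 one patient decides: 9/24 = 37.5% does not trigger and 10/24 = 41.7% does. For the lower 95% limit to exceed 40%, 15 of 24 (62.5%) would have to be dissatisfied.

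**4. The 20% rule, for comparison.** With n = 24 it triggers at 5. The observed 5/24 = 20.8% has an exact 95% CI of 7.1% to 42.2%, which covers both thresholds.

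**The case against.** **The confirmatory claim is already assigned elsewhere.** Sections 2.4 and 3.3 give it to the Wilcoxon–Mann–Whitney test. Section 3.3 calls the secondary analyses descriptive and says they serve to decide on modification of the app. Section 4 ties the expected benefit to a reduction in low-volume fractions. On this view the sentence in Section 3.3 is a loose clause in one of three statements of a product-development rule. This stands to the extent that a reader might infer that the satisfaction rule overrides the primary test, and the article nowhere says so. It does not remove the conflict, because the sentence is unconditional and stands in the statistical methods.

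**A liked but ineffective app.** A reader might also infer that such an app would pass. The rule runs one way only. Low dissatisfaction never establishes effectiveness, and an ineffective app would still have to face the primary test.

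**Patients who stop early.** A reader might infer that they are left out and are the dissatisfied ones. The article does not show either. The Abstract places the questionnaire on the last day of treatment, and a patient who stops early also has a last day. The expected 10% loss is defined by receiving fewer than 20 fractions, and the one trial stop described in Section 3.2.1 follows a radiotherapy delay. Neither concerns the app, so counting these patients as dissatisfied could record toxicity as dislike of the app.

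**Precision.** The thresholds have a stated origin, Section 4 concedes the small sample, and any rule on so few patients triggers about half the time when the true rate equals the threshold. That is fair: the 51% at a true rate of 40% is no special fault of this plan. The imprecision matters here because the rule leads to a statement about efficacy.

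**Conclusion.** The point holds as a fault in the wording of a decision rule. Section 3.3 lets a satisfaction rate decide a statement about bladder filling, and that statement can contradict a significant primary result with no means of reconciliation. This follows from the text alone and needs no assumption.

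The size of the imprecision rests on the assumed 24 to 27 answers and on independent binomial responses. Over that range, a true dissatisfaction rate of 30%, well under the threshold, still triggers the verdict in 10% to 16% of trials, and a true rate of 35% in 23% to 33%. With 24 answers the figures are 15% and 31%.

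The primary test, its sample size and its error control are unaffected.

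**What to change.** 1. Reword the >40% rule in the Abstract, Section 3.2.4 and Section 3.3 as one verdict on acceptability, for example: *not acceptable to patients in its present form*. Remove the reference to bladder filling.
2. State that every conclusion on bladder filling rests on the primary endpoint and its test alone.
3. Report the dissatisfaction rate with its denominator and exact 95% CI, beside the 20% and 40% thresholds.
4. Optional: a sensitivity analysis, labelled as worst case, that counts enrolled patients without an answer as dissatisfied. For example, 8/24 = 33.3% would become 11/27 = 40.7% if all three missing patients were so counted. It should not drive the verdict.

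The cost is a wording change and one interval, with no change to sample size, treatment or primary analysis. The sponsor gives up the use of the 40% rule for any statement on bladder filling, and the interval will show openly how imprecise the rate is. The change should be made before the data are seen.

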### 3.4. Data Protection

Data will be collected in accordance with the regulations set out in the Data Protection Act. All findings from the clinical trial will be stored on electronic data storage devices and treated with the utmost confidentiality. Organization measures will be taken in order to prevent the data from being communicated to unauthorized persons. Patients will only be identified via their individual patient numbers throughout the entire documentation and evaluation phase, and names or any information which would make the patient identifiable will not be used. For personal activation of the app for each study participant, Nextlabel OHG will receive the participant’s e-mail address. To ensure the protection of the participant’s e-mail address, a contract was concluded between the Sponsor (University Medical Center Schleswig-Holstein, UKSH) and Nextlabel OHG. This contract includes an approved data protection concept. Nextlabel will not have access to patient data that are not pseudonymized.

### 3.5. Data Management

Patient-related data are recorded pseudonymously, which means that a patient can be identified only by their unique number and their date of birth. A patient identification list is kept only in each center contributing patients to the REFILL-PAC-HYPO trial and will not be sent to the sponsor of the trial. For the collection and documentation of the data required for the REFILL-PAC-HYPO trial, specific forms are used.

Originals of the key documents of the REFILL-PAC-HYPO trial, including the documentation forms, will be kept by the sponsor of the trial for a period of at least 10 years after the completion of the final trial report. The principal investigator and the main investigator at each participating center, respectively, will keep administrative documents including correspondence with the responsible ethics committee and other authorities, patient identification lists, informed consent forms signed by the patients, copies of all documentation forms, and the general trial documents, including the study protocol, for at least 10 years after the completion of the final trial report. Original patient data need to be kept for the time period stipulated for the participating center, which is at least 10 years.

On-site monitoring is performed by the Centre for Clinical Trials, Lübeck, Germany, according to Good Clinical Practice and to the written standard operating procedures at the centers located in Germany. Visits include the initiation of the trial, visits during the period of the trial at intervals, which depend on the recruitment status and the quality of the data, and a close-out visit. Contributing centers outside Germany (e.g., in Denmark or Spain) are monitored in accordance with the national regulations in their own responsibility. Regular audits regarding the REFILL-PAC-HYPO trial are not planned. Since the trial does not meet the criteria for a study performed according to the German medicinal products act or medical device regulation, inspections by federal authorities are not scheduled.

The results of the REFILL-PAC-HYPO trial will be published in an international, peer-reviewed journal and are planned to be presented at scientific meetings or symposia. The corresponding reports and publications will be coordinated with the professional statistician involved. For these publications, the acronym REFILL-PAC-HYPO will be used.

## 4. Expected Results and Discussion

It is expected that the support provided by the reminder app will lead to a decrease in the mean value of radiation sessions with a bladder volume of <200 mL by 30% (to 11.2 sessions) when compared to the historical control group. Moreover, it is expected that the patients will be mostly satisfied with the reminder app, i.e., that the dissatisfaction rate will be below 20%. If this study shows that the reminder app helps to reduce the number of fractions with a bladder volume of <200 mL during moderately hypo-fractionated radiotherapy, a considerable number of patients with prostate cancer receiving this type of radiotherapy can benefit from such an app in the future.

Moderately hypo-fractionated radiotherapy lasting less than six weeks is becoming increasingly used for localized prostate cancer, since randomized trials have shown that this type of dose fractionation is not inferior to normo-fractionated radiotherapy (overall treatment time from 7.5 to 8 weeks) [4,5,6]. Only the CHHiP trial included patients with prostate cancers from all three risk groups, including high-risk tumors, which represented 12% of the trial cohort [4]. The other two trials were limited to intermediate-risk and low-risk tumors, respectively [5,6]. Thus, moderately hypo-fractionated radiotherapy is mainly used for patients with intermediate-risk and low-risk tumors. In two of the randomized trials, a dose fractionation regimen of 20 × 3.0 Gy over four weeks was used [4,5]. Like other fractionation regimens for prostate cancer, moderately hypo-fractionated radiotherapy can lead to radiation cystitis. Since the risk of grade ≥ 2 acute urinary toxicity, including radiation cystitis, is markedly increased if the bladder volume is <200 mL, it is very important to keep the bladder volume ≥ 200 mL during as many radiotherapy sessions as possible [8,10]. To improve bladder filling status during EBRT for prostate cancer, several studies have investigated the potential benefit of so-called drinking protocols requesting patients to drink a certain amount of water at a specific time before each radiotherapy session and before CT simulation [10,11,12,15,16,17,18,19,20,21,22,23,24,32]. However, following these protocols can be challenging for mostly elderly or even very elderly patients. The question of whether these patients may benefit from support by a reminder app has been raised. Such an app would remind patients to drink water at a pre-selected point in time. The REFILL-PAC-HYPO trial investigates an app reminding patients who are receiving moderately hypo-fractionated radiotherapy for localized prostate cancer to drink 300 mL of water 45 min before each treatment session. The trial evaluates whether this app reduces the number of fractions with a bladder volume of <200 mL during the radiotherapy course when compared to a historical control group of patients treated with moderately hypo-fractionated radiotherapy who were not supported by a reminder app.

Our previous study identified significant differences between patients with a pre-radiotherapy bladder volume of <200 mL and those with a volume of ≥200 mL regarding the number of fractions with a volume of <200 mL during a radiotherapy course of 20 fractions [13]. The mean and median numbers of fractions with a volume of <200 mL were 16.0 vs. 7.9 and 19.0 vs. 8.0, respectively. As a consequence, the REFILL-PAC-HYPO trial is limited to patients with a pre-radiotherapy bladder volume of <200 mL, since these patients are much more likely to benefit from the reminder app. For the comparison of the REFILL-PAC-HYPO cohort to the historical control group, a matching procedure is performed that considers nine patient- and tumor-related factors.

However, this study has several limitations that need to be considered when interpreting its results when they become available. Its single-arm design cannot exclude the Hawthorne effect, the small sample size may result in an insufficient statistical validity, and the historical control group may have unmeasured confounders due to retrospective data. The fact that patients in the REFILL-PAC-HYPO cohort must own a smartphone and be capable of using the app bears the risk of a selection bias. The urinary bladder is contoured by experienced staff members, and the bladder volume is automatically calculated by the planning system. However, the risk of an observer bias remains, since investigators know which patients use the reminder app. Blinding is not possible, since all patients participating in the prospective trial are supported by the app. In general, this lack of randomization could impact the trial’s internal validity.

## Figures and Tables

**Table 1 clinpract-15-00040-t001:** Inclusion and exclusion criteria for the REFILL-PAC-HYPO trial.

Inclusion criteria	Histologically proven prostate cancer Indication for hypo-fractionated radiotherapy Possession of and ability to use a smart phone Bladder volume at CT simulation <200 mL Age ≥ 18 years Written informed consent Capacity of the patient to contract
Exclusion criteria	Radiotherapy of pelvic lymph nodes Expected non-compliance

**Table 2 clinpract-15-00040-t002:** Timeline of enrolment, interventions, and assessments. ^#^ during each radiotherapy session.

	**Prior to** **radiotherapy**	**Weekly during the** **course of radiotherapy**	**At the end of radiotherapy**
Medical history and concomitant diseases	X		
Demographic data	X		
Concomitant medication	X		
Systemic anticancer treatment	X	X	X
Patient characteristics	X		
Performance status	X		X
Radiotherapy (given as planned ?)		X	X
Informed consent	X		
Assessment of adverse events and serious adverse events		X	X
**Bladder volume according to Cone-Beam Computed Tomography**	**X**	**X ^#^**	**X**
Experience with smartphones	X		
**Satisfaction with the reminder app**			**X**
**Impact of the reminder app on the use of health technology**			**X**

## Data Availability

Further information regarding this trial is available at clinicaltrials.gov (identifier: NCT06784115).

## Abbreviations

The following abbreviations are used in this manuscript:

BMI	Body Mass Index
CBCT	Cone Beam Computed Tomography
CT	Computed Tomography
CTCAE	Common Terminology Criteria for Adverse Events
EBRT	External Beam Radiotherapy
IQR	Interquartile Range
SD	Standard Deviation
VMAT	Volumetric-Modulated Arc Therapy
